#### Exclusion criteria

• Children whose medical history precludes inclusion (i.e. those with a history of hospitalisation for asthma, or severe allergies, or allergy to Elastoplast; determined from Medical History Form completed by parents)

• Children with known sensitivity to colophony (kolophonium), or any of the product ingredients (e.g. methylacrylate in PFS; determined from Medical History Form completed by parents)

• Children with ulcerative gingivitis or stomatitis (determined at baseline examination)

• Children with any facial or oral infections e.g. cold sores (determined at baseline examination)

• Children with any abnormality of the lips, face or soft tissues of the mouth that would cause discomfort in the provision of PFS/FV (determined at baseline examination)

• Children who are showing obvious signs of systemic illness (e.g. colds, ‘flu’, chicken pox etc.) (determined at baseline examination)

• Children currently participating in another clinical trial involving an investigational medicinal product (IMP; determined from Medical History Form completed by parents).

### Trial interventions

The two technologies to be evaluated in this trial (PFS and FV) are well established and have been used routinely to prevent dental caries for several decades. Eligible participants will be randomised to receive either PFS or FV, and will remain on the intervention to which they have been randomised for the duration of the study.

#### Pit and fissure sealant (PFS)

The PFS used for evaluation in the study is Delton® Light Curing Opaque Pit & Fissure Sealant (Dentsply Ltd; CE0086). We chose this product as a commonly used PFS and that used in the existing community dental programme. PFS will be supplied as 2.7 ml bottles for multiple applications and applied topically as a thin layer to the occlusal surface of eligible teeth.

Initial application of PFS will occur within 2 weeks of the baseline dental examination, and will be performed by a suitably qualified and trained dental hygienist according to the conventional clinical protocol established by the CDS. The condition of the PFS will be re-examined at 6, 12, 18, 24, and 30 months, and will be re-applied if the existing sealant has become detached, or if attachment is considered insufficient. Newly erupting FPMs will have PFS applied in the course of the trial.

All applications of PFS will be documented on a treatment record form, which will capture the date, batch number, patient ID number and number of sealants (i.e. teeth) applied.

#### Fluoride varnish (FV)

The FV used for evaluation in the study is Duraphat® 50 mg/ml dental suspension (Colgate-Palmolive (UK) Ltd; PL 00049/0042), equivalent to 22,600ppm fluoride. We chose this product as a commonly used FV and that used in the existing community dental programme. FV will be supplied as 10 ml tubes for multiple applications and applied topically as a thin layer to the pits, fissures and smooth surfaces of eligible teeth. As per the Duraphat Summary of Product Characteristics (SmPC), dosage per single application will not exceed 0.4 ml.

Initial application of FV will occur within 2 weeks of the baseline dental examination, and will be performed by a suitably qualified and trained dental hygienist according to the conventional clinical protocol established by the CDS. FV will be re-applied at 6, 12, 18, 24, and 30 months.

All applications of FV will be documented on a treatment record form, which will capture the date, batch number, patient ID number and number of applications (i.e. teeth) performed.

Where children enrolled onto the study are registered with a General Dental Practitioner (GDP), the GDP will be informed of the child’s participation in the study and requested to not apply either PFS/FV (or other fluoride-based treatment) for the duration of the trial.

### Outcome measures and follow-up of study participants

Participant flow through the trial is shown in Figure 2.

**Figure 2 F2:**
[figure not shown]
Participant flow through the trial.

### Clinical evaluation

Participants will undergo a clinical examination using standard visual caries diagnosis (both enamel and dentinal level) at baseline and 12, 24 and 36 months by a trained and calibrated dentist, blind to treatment allocation. All fully-erupted non-carious first permanent molars (FPM) will be treated.

#### ICDAS caries assessment

Caries status will be assessed at baseline for all children considered eligible. Caries status will be assessed and recorded by trained and calibrated dentists using conventional diagnostic caries criteria at the d1/D1- d3/D3 level in accordance with nationally recognised diagnostic criteria [12]. Data will be recorded using charts specifically designed for collection of ICDAS dental codes [13].

In addition to baseline, a clinical examination including ICDAS caries assessment will be performed at 12 month intervals for 36 months.

As part of the annual caries assessment approximately 5% of study participants will be re-examined to determine intra-examiner reproducibility.

#### Medical history and caries risk related habits

The medical history of the child will be ascertained by asking the parents to complete a medical history form, which will collect data specifically relating to: allergies; asthma (including whether this has resulted in hospitalisation); sensitivity to constituents of either PFS or FV; if the child is currently participating in a clinical trial involving an IMP. Whether or not the child is registered with a General Dental Practitioner will also be ascertained.

Following enrolment onto the trial, any changes to the child’s relevant medical history (as described above) will be identified by enclosing a brief Medical History Follow-Up Form with the postal questionnaires sent to parents on an annual basis during the trial.

For children deemed eligible to participate in the trial, information relating to caries risk related habits will be obtained via a postal questionnaire sent to parents at baseline, 12, 24 and 36 months post treatment.

### Health economics assessment

The economic analysis will estimate the costs of providing the PFS versus FV, and the consequences of the scheme for the NHS, children and their families, education and society.

In principle the following analyses will be undertaken:

• Costs for each trial participant will be calculated. Number and frequency of service utilisation will be multiplied by the relevant unit cost (derived from published sources: [14,15] to produce a total cost per participant

• Travel costs and other costs to families associated with provision of PFS and FV will be collected using structured questions

• Assessment of the total cost of PFS and FV including potential costs of treatments avoided.

The identification and collection of costs will be undertaken using the following methods.

#### National health service (NHS)

Data on the use of community health dental resources will be collected through structured interviews with key relevant dental and finance staff and the main trial team. A micro-costing exercise will also be undertaken to assess direct costs to the NHS. This will include staff resources (e.g. number, grades of staff), treatment/appointment duration; equipment and materials used. These will be logged on resource utilisation recording sheets at each clinic and costed using published unit costs [14,15] and list prices e.g. British National Formulary [16].

#### Children and families

The costs to families (including the child) will be collected using a Parental Resource Utilisation (PRU) questionnaire, which will be combined with questions relating to Caries Risk Related Habits to form a single postal ‘Dental Health’ questionnaire to be completed by parents. This brief questionnaire will capture information on any time away from work/other paid activities to attend the child’s appointment or other dental appointments; any medication for dental-related problems and normal dental hygiene practice at home for the child. In addition, parental occupation will be captured. As with Caries Risk Related Habits, this information will be collected at baseline, 12, 24 and 36 months post treatment.

The health-related quality of life (HRQoL) of children will be measured using the CHU-9D questionnaire [17,18]. The CHU-9D questionnaire will be sent to parents with instructions to ask the child to complete it, providing assistance if required. CHU-9D questionnaires will be sent out at 12, 24 and 36 months following the initial treatment. Utility values will be calculated to derive quality adjusted life years (QALYs).

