### Time plan for the SoV trial

Participant recruitment began in July 2011 and is planned to continue to until December 2012. Children will be followed up for three years and therefore the last child will have their final follow-up assessment in December 2015.

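### QALYs are derived from the CHU-9D, which is first sent 12 months after treatment: the first year of utility must be assumed, and adjustment for baseline utility is lost

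*Protocol article*

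**What the plan says.** The protocol article, under Health economics assessment, Children and families, names one instrument for the child's quality of life: "The health-related quality of life (HRQoL) of children will be measured using the CHU-9D questionnaire". It is posted to parents, and the schedule is explicit: "CHU-9D questionnaires will be sent out at 12, 24 and 36 months following the initial treatment". Its purpose is also explicit: "Utility values will be calculated to derive quality adjusted life years (QALYs".

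The preceding paragraph of the same section describes the Dental Health questionnaire, which combines parental resource use with caries-risk habits. Its schedule is different: "As with Caries Risk Related Habits, this information will be collected at baseline, 12, 24 and 36 months post treatment". The section on medical history and caries-risk habits agrees that this information is "obtained via a postal questionnaire sent to parents at baseline, 12, 24 and 36 months post treatment".

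On timing, the time plan states that "Children will be followed up for three years", and the sealant section states that "Initial application of PFS will occur within 2 weeks of the baseline dental examination". The varnish section has the same two-week limit. Twelve months after treatment is therefore about twelve months after baseline.

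**The concern.** A QALY total over follow-up is normally the area under the utility curve from entry. With utilities at 12, 24 and 36 months only, the curve has no starting point, and the area for the first year rests on an assumption that the article does not state. The 12-month form cannot stand in as a baseline, because it comes after treatment has begun.

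Two things follow. The QALY difference depends on how the first year is filled in. In addition, a chance difference in utility at entry can be neither seen nor adjusted for. Minimisation balances gender and baseline caries, not utility.

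This is not detail that a condensed article leaves to a fuller document. The time points are stated, and two schedules for the same parents stand side by side, of which only the utility instrument lacks baseline. A later analysis plan can choose an assumption, but it cannot recover data that were never collected. Relative cost-effectiveness belongs to the trial's overall aim and is a secondary objective.

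**Working it through.** The plan gives no figure for utility or QALYs, so there is none to reproduce. The schedule and follow-up come from the article. The utility gaps, SDs and correlations below are assumptions, as is the area-under-the-curve (trapezoid) method, which the article does not name.

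**Coverage.** Trapezoid weights in years:

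| Schedule | Month 0 | 12 | 24 | 36 | Total |
|---|---|---|---|---|---|
| As written | – | 0.5 | 1 | 0.5 | 2.0 |
| With baseline | 0.5 | 1 | 1 | 0.5 | 3.0 |

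The uncovered part is 12/36, one third of the follow-up.

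**Dependence on the convention.** Assume a between-arm utility gap of 0.01 at 12, 24 and 36 months.

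- Months 12 to 36 only: 0.5 × 0.01 + 1 × 0.01 + 0.5 × 0.01 = 0.020.
- Equal baselines in both arms: 0.5 × 0 + 0.01 + 0.01 + 0.5 × 0.01 = 0.025. The common level cancels from the difference.
- 12-month value carried back to entry: 3 × 0.01 = 0.030.

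The same data give results whose largest is 0.030/0.020 = 1.5 times the smallest.

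**An unseen baseline gap b.** The difference becomes 0.025 + 0.5 × b. For b from -0.02 to +0.02 it runs from 0.015 to 0.035.

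**Plausible size of b.** The article expects 920 × 0.92³ × 0.95 ≈ 680 children at the final examination, about 340 per arm. With an assumed utility SD of 0.10 (range 0.08 to 0.15), the standard error of the baseline difference is 0.10 × √(2/340) ≈ 0.008 (0.006 to 0.012). The chance of a gap beyond 0.01 in either direction is then about 19% (10% to 38%). Incomplete postal return would raise these figures.

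**Precision forgone.** Let r be the correlation between baseline utility and the later utility summary. Regression adjustment removes a fraction r² of the variance. For assumed r of 0.3 to 0.6 this is 0.3² = 9% to 0.6² = 36%. The gain applies to children who have a baseline form.

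**The case against.** The strongest reply is that an incremental QALY needs the entry difference between arms, not the entry level. Children are randomised individually 1:1, about 460 per arm, so that difference is zero in expectation. A common baseline then fills the first year without expected bias. This stands. A reader might infer that the missing baseline biases the comparison, and the design does not support that.

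A reader might also infer that no baseline adjustment is possible. Only adjustment for baseline utility is lost. Gender, baseline caries and the baseline questionnaire items remain available.

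A third tempting inference is that an entry gap of 0.01 costs 0.01 × 3 = 0.03 QALY. That needs the gap to persist undiminished. If baseline utility correlates 0.3 to 0.6 with each later utility (equal SDs assumed), the expected later gap is 0.003 to 0.006. The area is then 0.5 × 0.01 + 2.5 × 0.003 = 0.0125 up to 0.5 × 0.01 + 2.5 × 0.006 = 0.020.

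Nor do the documents show that such a gap would decide a cost per QALY. The text shown states no incremental cost per QALY, no QALY horizon and no expected QALY difference, and it also names Quality Adjusted Tooth Years as an economic outcome.

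Two practical points also stand. The baseline questionnaire goes to parents of children already found eligible, and treatment follows within two weeks of the examination, so a posted form may come back after treatment has started. The participant-flow figure is not shown, so a different schedule there cannot be excluded.

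**Conclusion.** The point holds as a cheap improvement to a secondary economic measure. On the stated schedule, utilities are measured over 2 of the 3 years, the first year rests on an assumed starting value, and adjustment for baseline utility is unavailable. No bias is expected. The loss is precision, protection against chance imbalance, and a result that moves with an unstated convention: 0.020 to 0.030 QALY for an assumed constant gap of 0.01, plus 0.5 × b for any hidden entry gap. The 9% to 36% variance reduction rests wholly on the assumed correlations. The primary clinical outcome and its sample size are untouched.

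**What to change.** 1. Add the CHU-9D to the baseline pack for every child still to be recruited; the time plan has recruitment running to December 2012. Ask for completion before first treatment and record the completion date, so that late forms can be identified.
2. Derive QALYs by area under the curve from baseline, with regression adjustment for baseline utility.
3. For children already enrolled, or with no returned baseline form, use a common baseline across arms, justified by randomisation, or impute it within that model. State the choice in advance. If recruitment has closed, this step and the next are what remain.
4. Report QALYs for months 12 to 36 only as a sensitivity analysis.

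The cost is one nine-item form in a mailing that already goes out, and a minor amendment. Some baseline forms will be missing or late, younger children may need parental help, and children already enrolled cannot be covered.

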#### Education

Data on the use of school resources will be collected through the administration of a structured questionnaire with the headteacher from participating schools. This will include time of the child away from classroom/usual school activities, school administration time, teacher time, other school personnel time and other school resources utilised. This information will be collected alongside the collection of information via the headmaster questionnaire survey on the acceptability, feasibility and sustainability of the programme in Schools.

#### Implementation costs

Costs of implementing the interventions are not applicable to this study as the MDC is already established. However, the analysis will take into account the depreciation costs of the clinic over the trial period and beyond as part of the sensitivity analysis.

#### Research costs

These will be separated from the other costs incurred to provide clarity. The research costs incurred as a result of establishing the study, training, running the evaluation, completing questionnaires will be collected through discussion with the main trial team.

### Process evaluation

The process evaluation for the study will address two secondary outcomes: treatment acceptability and implementation in a community setting. Trial implementation will also be examined.

Treatment acceptability will be assessed in three ways.

During the clinical placement of the technologies under investigation, the indicators of patient acceptability/adverse outcomes: vomiting, crying, gagging, excessive arm/leg movements and other signs of distress [19] will be recorded by both the dental hygienist and dental nurse using an observational scale. Treatment acceptability will also be assessed from the child’s perspective through a Delighted-Terrible Faces (D-T) scale, completed by all children in the MDC immediately following the initial application of PFS/FV, and at each follow up visit. This is a modified version of the Delighted-Terrible Faces (D-T) Scale [20,21]. This scale has a child-friendly format with a range of ‘delighted’ to ‘terrible’ faces arranged in a five-point Likert scale, with minimal text. These scales will be analysed statistically as part of the secondary outcomes analysis.

In addition, qualitative interviews will be conducted with a subsample of children and parents to collect data on the quality of the experience of receiving sealant or varnish treatment, and to understand factors affecting acceptability such as taste, length of treatment, treatment setting and prior family dental experience. Quantitative data will be triangulated with each other and also with parent and child interviews. Children and their parents from each trial arm will be interviewed in order to compare the experience of PFS and FV treatment, and interviewees will also be drawn from higher and lower deprivation areas in order to examine the impact of socio-economic status on participant perceptions of the dental treatment.

The process evaluation interviews will also explore the implementation of the Seal or Varnish programme in a community setting, addressing factors such as the utility of using a school setting to deliver preventative treatment and trial implementation covering factors affecting recruitment, retention and potential bias. These data will be used to illuminate trial outcomes.

#### Interviews with children

A sample of schools participating in the trial will be selected for the purpose of conducting interviews with children receiving treatment. Schools will be stratified by size and free school meal (FSM) entitlement. Larger schools will be selected to ensure an adequate number of children can be sampled for paired interviews. Schools will also be sampled from the upper and lower FSM quartiles in order to collect date on children from higher and lower deprivation areas. Within each school, children will be stratified by trial arm and also by level of treatment acceptability (above and below the mean) based on their D-T scale responses. In total, 48 children will be interviewed face-to-face in a school setting, 24 in each trial arm. This sampling will enable three domains (deprivation, measured by FSM; trial arm and acceptability level) to be analysed both within each domain (e.g. factors associated with high and low acceptability) but also an investigation into how the three domains intersect with each other. The staff member(s) responsible for trial aspects at each school will assist in inviting the sampled children to attend a face-to-face interview in pairs; this method should ensure children feel more confident and relaxed in interviews. Interviews will be conducted with children in a school setting up to two weeks after their first and last treatment to ensure children will have a reasonably accurate recall of their experience of treatment. Interviewers will be provided with information about the initial D-T scale results for each interviewee prior to the interviews to inform how questions are asked. The scale results will not be discussed during interviews, however, to ensure confidentiality since the interviews will be in pairs.

#### Interviews with parents

Parents of sampled children will be interviewed, with 24 parents interviewed in each trial arm. Parents will be interviewed by telephone four to six weeks after their child’s first and last treatments where possible. Where parents of sampled children cannot be contacted, additional parents of participating children will be sampled to ensure an overall total of 48 parents are interviewed.

#### Questionnaires/interviews with schools

All schools will be asked to complete a questionnaire at the beginning of the study regarding their experience with implementation of the trial. At the end of the study a number of schools will be purposively sampled based on responses to the questionnaires. The member of staff within each participating school who has the most involvement in the trial will be invited to take part in a telephone interview to investigate the impact of the trial on the school. The implications of this for the acceptability and feasibility of the trial in a community setting will be determined.

#### Interviews with the dental team

The dental team delivering the treatment in schools will be interviewed annually in order to assess how the trial is implemented, factors which promote or impede implementation, perceptions of patient acceptability, and experiences of working with schools.

#### Interviews with non-participants

Up to 20 withdrawing parents will be contacted by letter seeking consent for a telephone interview. Data from these interviews will be compared by trial arm in order to examine reasons for leaving the study and any possible bias this might introduce. A sample of up to 20 non-responding and up to 20 non-consenting parents will also be contacted for interview. Data from these interviews will be used to explore any potential bias introduced into the study and to assess contextual factors affecting recruitment into the programme.

### Randomisation

Randomisation of participants will be stratified by school and balanced for gender and baseline caries levels using minimisation in a 1:1 ratio for treatments. An additional random component will be added to the minimisation algorithm [22] such that it is not completely deterministic. Randomisation will be undertaken by SEWTU remote from the trial sites.

